### Study outcomes

#### Smoking cessation: assessed on two occasions

Self-reported, prolonged complete abstinence from smoking (a) between six weeks after enrolment in the scheme and prior to childbirth; and (b) between childbirth and six months later. All women lost to follow-up will be assumed to have resumed smoking. This definition gives women a cessation induction period of up to six weeks, although we expect many women will establish abstinence sooner than this.

These are two outcomes requiring the following different measures:

(a) between six weeks after enrolment in the scheme and prior to childbirth

i. self reported smoking cessation for at least 24 hours at six weeks after enrolment in the scheme, validated by exhaled CO measurement of less than or equal to 6 ppm;

ii. self reported complete abstinence from 6 weeks after enrolment to 36 weeks gestation, validated by salivary cotinine less than 15 ng/ml at 36 weeks. In addition, there must be no reported lapses and a record that all CO readings taken between these dates indicate non-smoking status. All women lost to follow-up will be assumed to have resumed smoking.

(b) between childbirth and six months later

i. self reported smoking cessation for at least 24 hours two days after delivery, validated by exhaled CO measurement of less than or equal to 6 ppm and salivary cotinine less than 15 ng/ml, in keeping with local practice.

ii. self reported complete abstinence from two days after enrolment to six months postpartum, validated by salivary cotinine less than 15 ng/ml at six months. In addition, there must be no reported lapses and a record that all CO readings taken between these dates indicate non-smoking status [27]. All women lost to follow-up will be assumed to have resumed smoking.

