### Measuring smoking cessation

To assess the effectiveness of the intervention it is necessary to have an accurate measure of smoking cessation. For most people who smoke cigarettes and have difficulty quitting (addicted smokers), only the state of complete abstinence is sustainable as occasional smoking leads to reinstatement of fulltime smoking. The outcome of choice for smoking cessation studies should therefore be prolonged or continuous abstinence [27,28]. In particular, this is the only outcome known to be associated with health benefits.

Biochemical verification tests, such as testing CO levels or nicotine metabolites such as cotinine, are the preferred methods of validating smoking cessation in clinical studies such as this [29]. Testing for CO levels using a breath test assesses smoking in the preceding one to four hours whereas cotinine analysis from blood, urine or saliva samples can measure exposure to smoking in the preceding few days [29]. However, testing for cotinine in body fluids is more complex to administer and expensive to analyse than testing CO levels.

In the current study we will use cotinine from urine samples to confirm smoking status at recruitment, and from saliva samples to verify abstinence both at delivery and at six months post-partum. Cotinine testing will also be used once during pregnancy (at around 28 weeks) to compare with CO measurements taken at the same time. For practical reasons, CO tests alone will be used on all other occasions when women attend to receive incentive payments.

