##### Other measures of smoking status

Self reported prolonged abstinence from smoking assessed by self-reported smoking cessation six weeks after enrolment in the scheme, validated by CO reading, and self report smoking cessation at 28 weeks gestation, validated by salivary cotinine less than 15 ng/ml.

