#### Estimating the adverse effects of using incentives to achieve quitting

a) *delay in quitting smoking to enrol in an incentive scheme*: There are concerns that the estimated 11% of women who quit smoking upon learning they are pregnant may delay quitting until they can enrol in the incentive scheme. We will estimate this effect by comparing the self-reported smoking status of women during the time the scheme is running, with that recorded for the preceding 12 months. While this is open to the usual biases associated with historic controls, it will provide some indication of whether the scheme has delayed quitting.

b) *gaming i.e. false reporting of smoking status:* Two types of gaming are possible;

i) *To gain entry to the scheme (i.e. non-smokers acting as smokers).* We will estimate this in two ways: first, using historic controls (by comparing the proportion of women who claim to smoke at the outset of the study with the proportion who reported being smokers in the year prior to the start of the scheme); second, by assessing the proportion of women claiming to smoke with levels of urinary cotinine compatible with non-smoker status. Our inclusion criteria are set to minimise entry to the scheme by non-smokers.

ii) *To gain an incentive (i.e. smokers acting as non-smokers).* We will estimate this by validating CO records and self-reported smoking status against measurement of cotinine collected at 28 weeks gestation, 36 weeks gestation and 2 days after delivery and 6 months post-partum.

The two primary outcomes of this study are:

smoking cessation at delivery; and,

false reporting of smoking status to gain an incentive.

The remaining outcomes will be considered secondary.

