**Figure 1 F1:**
[figure not shown]
Flow of recruitment process.

All women will be offered the standard support by the SSS regardless of whether they take part in the financial incentive scheme.

Pregnant women who meet the inclusion criteria will be enrolled into the study. Provided they have read and understood the participant information sheet and had the chance to have any questions answered, signed consent will be sought for the following:

(a) participation in the scheme;

(b) collection and analysis of one urine and four saliva samples for cotinine estimation: two during pregnancy (28 and 36 weeks gestation) and two post-partum (two days after delivery, and six months post-partum);

(c) completion of a questionnaire to assess predictors of smoking cessation.

Once consent has been given, the support worker will encourage the participant to set a quit date and issue them with a ‘programme passport’ which will contain their photograph for identification and the date, test result and voucher value of each visit.

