### Biological samples taken to assess quitting and gaming

A urine sample is tested at the enrolment visit, using a dipstick test, to assess eligibility for the scheme, with urinary cotinine concentrations equal to or more than 1.5 mg/ml sufficient for enrolment.

Saliva samples are collected by the support worker at 28 weeks gestation, 36 weeks gestation, 2 days post delivery and amongst women reporting cessation, at 6 months post delivery and analysed by a nationally accredited laboratory for cotinine concentrations. For women reporting current use of nicotine replacement therapy, anabasine, a tobacco specific alkaloid, will be analysed.

In addition to being used to biochemically verify quitting, the results of these analyses will be used to estimate the proportions of women reporting having quit who have not. Both women and the support worker will remain blinded to the test results unless a woman requests her result. Women proven to be smoking on any of these extra tests (i.e. those using saliva as opposed to CO) will not be confronted with this, withdrawn from the scheme or refused vouchers. The aim is to estimate the extent of the gaming that is occurring. It is possible for women to abstain for a few hours and pass a CO test but such women would be shown to be smokers by salivary cotinine.

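### The primary quit outcome leaves out the 28-week salivary cotinine, so a woman enrolled before about 22 weeks can be a prolonged abstainer under one primary outcome and a false reporter under the other

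*Protocol article*

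**What the plan says.** Under Study outcomes, the section on smoking cessation sets two parts for the pregnancy outcome (a). Part (a)i asks for CO-validated cessation of at least 24 hours at six weeks after enrolment. Part (a)ii asks for "self reported complete abstinence from 6 weeks after enrolment to 36 weeks gestation, validated by salivary cotinine less than 15 ng/ml at 36 weeks". It adds that "there must be no reported lapses and a record that all CO readings taken between these dates indicate non-smoking status". No other cotinine result is named.

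The Enrolment section seeks consent for saliva samples, "two during pregnancy (28 and 36 weeks gestation") and two after delivery. The 28-week result is given three uses:

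- Measuring smoking cessation: "Cotinine testing will also be used once during pregnancy (at around 28 weeks) to compare with CO measurements taken at the same time".
- Other measures of smoking status, a separate prolonged-abstinence measure that starts at the same six-week point and ends with "self report smoking cessation at 28 weeks gestation, validated by salivary cotinine less than 15 ng/ml".
- Estimating the adverse effects of using incentives, where the method for false reporting to gain an incentive is given as "validating CO records and self-reported smoking status against measurement of cotinine collected at 28 weeks gestation, 36 weeks gestation and 2 days after delivery"; a six-month sample is added to these.

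That last section closes with a list introduced by "The two primary outcomes of this study are": smoking cessation at delivery, and false reporting of smoking status to gain an incentive.

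**The concern.** Outcome (a)ii is a claim about an interval, but its only cotinine check is at the end of that interval. A cotinine result from the middle is available and is not consulted. The article itself explains why CO cannot stand in for it. Measuring smoking cessation gives CO a look-back of one to four hours and cotinine a few days. The section on biological samples says: "It is possible for women to abstain for a few hours and pass a CO test but such women would be shown to be smokers". The test it means is salivary cotinine.

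Two things are at stake. First, the two primary outcomes can classify the same woman in opposite ways over the same weeks. Second, the error in the quit rate runs in one direction only: ignoring a positive mid-interval sample can add apparent quitters and never remove them. The study's main product is the estimate itself, which is meant to inform practice and later trials.

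**Working it through.** **1. The plan's own precision figure.** Inputs from Precision estimation: quit rate 24%, 150 enrolled.

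- Expected quitters: 0.24 × 150 = 36.
- 95% half-width: 1.96 × √(0.24 × 0.76 / 150) = 0.0683, or 6.8 points. This matches the stated ±7%, and nothing in that figure is disputed.

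**2. Who is affected.** The abstinence interval opens six weeks after enrolment, so a 28-week sample lies inside it only if enrolment was before about 28 − 6 = 22 weeks. The footnote to Table 2 describes a start at about 12 weeks. For such a woman the interval runs from week 12 + 6 = 18 to week 36. If she also quits at about week 12, Table 2 places eight CO visits in it (visits 8 to 15, at 6 to 24 weeks after quitting). Visit 13, 16 weeks after quitting, falls at week 28, and an unbroken run earns £20 there.

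**3. One woman, three measures.** She enrols at 12 weeks, denies all lapses, passes every CO test, has a 28-week sample that indicates smoking, and is below 15 ng/ml at 36 weeks.

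| Measure | What it requires | Her result |
|---|---|---|
| Outcome (a) | CO-validated at six weeks; no admitted lapse; all CO negative; cotinine below 15 ng/ml at 36 weeks | Met: prolonged abstainer |
| Other measures of smoking status | CO-validated at six weeks; cotinine below 15 ng/ml at 28 weeks | Not met |
| False reporting to gain an incentive | Self-report and CO checked against cotinine, including at 28 weeks | False reporter |

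The first two rows start at the same point. She fails the shorter abstinence period and passes the longer one that contains it, which is not coherent. The first and third rows are the conflict between primary outcomes.

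The postpartum outcome (b) does not have this gap. It requires salivary cotinine below 15 ng/ml both two days after delivery and at six months, so both samples scheduled in its interval count.

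**4. Size.** Each such woman changes the rate by 1/150 = 0.67 points. The documents do not say how many of the 36 there would be. The counts below are hypothetical and only show sensitivity (Wald 95% intervals):

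| Women removed from 36 | Rate | 95% interval |
|---|---|---|
| 0 | 36/150 = 24.0% | 17.2 to 30.8 |
| 2 | 34/150 = 22.7% | 16.0 to 29.4 |
| 4 | 32/150 = 21.3% | 14.8 to 27.9 |
| 7 | 29/150 = 19.3% | 13.0 to 25.7 |
| 11 | 25/150 = 16.7% | 10.7 to 22.6 |
| 18 | 18/150 = 12.0% | 6.8 to 17.2 |

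Even with half of the apparent quitters removed, the interval excludes 0%, which is the criterion in Data analysis.

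**The case against.** The strongest counter-argument is textual. The section on biological samples says in general terms that the saliva analyses serve to verify quitting as well as to estimate false reporting, and the 28-week sample is among those it lists. On that reading the 28-week result already bears on quitting. This does not carry the point. The outcome definition names only the 36-week sample, and the 28-week sample has a measure of its own. If the sponsor did intend it to count, the general sentence and the specific definition disagree and still need to be aligned.

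Other objections stand and limit the point:

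- **The information is not lost.** The 28-week result feeds a primary outcome and a separate abstinence measure. What is missing is its link to the quit numerator.
- **Persistent smokers are already caught.** A reader might infer a large bias from the study cited under Unintended perverse effects (38% abstinent by CO, 7% by cotinine in the incentivised group). The documents do not support that. Outcome (a)ii already requires a cotinine result at 36 weeks, so a woman still smoking then fails. The gap concerns only women whose 28-week sample indicates smoking, who passed everything else and were negative at 36 weeks. The cited figures say nothing about the size of that group.
- **Raised cotinine is not always smoking.** Nicotine replacement is part of typical NHS support, and the plan provides anabasine for women reporting its use. A bare cotinine rule at 28 weeks could fail an abstinent woman.
- **Late enrolment is exempt.** For enrolment after about 22 weeks, smoking at 28 weeks falls within the allowed induction period.

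**Conclusion.** The point holds as a flaw in the definition of a primary outcome. On the text as written, a woman enrolled before about 22 weeks whose 28-week sample indicates smoking can be counted as completely abstinent across that date, while the other primary outcome counts her as a false reporter. The bias is upward, at 0.67 points per woman on 150 enrolled. Its total cannot be computed from the documents.

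A reader might go further and infer that the quit result would be unsound or the study's conclusion reversed. The documents do not support that. There are no formal tests, the only criterion is whether the interval excludes 0%, and that is unlikely to change at the planned rate. The correction is worth making because it is simple and the estimate is what others will use, but the study does not depend on it. The verdict rests on the planned 24% of 150 and on reading the outcome section as the governing definition. The primary list's label refers to delivery, whereas outcome (a) ends at 36 weeks; on either reading the 28-week result is not a condition.

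**What to change.** Add one sentence to (a)ii: every salivary cotinine taken between six weeks after enrolment and 36 weeks' gestation must indicate non-smoking, meaning below 15 ng/ml, or a negative anabasine result for women reporting nicotine replacement. Samples taken before the six-week point do not count. This follows the rule already applied to CO, where every reading in the interval must be negative.

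State also that a missing 28-week sample is not by itself a failure. This is distinct from loss to follow-up, which the plan already counts as smoking. It does make classification depend partly on whether a sample was obtained, so report the rate without the 28-week condition alongside as a sensitivity analysis, with the number of missing samples.

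The sample is already collected and assayed. Vouchers, visits and the blinding of women and the support worker are untouched, because only the evaluation team's classification changes. The cost is a possibly slightly lower headline quit rate.

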24	6 weeks after delivery	30 + 1	468
25	8 weeks after delivery	31 + 1	500
26	10 weeks after delivery	32 + 1	533
27	12 weeks after delivery	33 + 1	567
28	14 weeks after delivery	34 + 1	602
29	16 weeks after delivery	35 + 1	638
30	20 weeks after delivery	36 + 1	675
31	24 weeks after delivery	37 + 1	713
32	28 weeks after delivery	38 + 1	752

^1^ This table shows the maximum that can be earned by a woman who starts on the scheme at about 12 weeks gestation and who attends all scheduled visits and is verified as not smoking at each visit. A woman starting quitting later in pregnancy would start with Visit 1 in terms of the incentive on offer. If she delivered shortly after Visit 12, her post delivery visit is paid at the rate of Visit 13. The maximum number of visits this woman could make is 28.

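### The primary outcome is named and headed as abstinence to delivery, but its operative criterion ends and is verified at 36 weeks gestation

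*Protocol article*

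**What the plan says.** Five places in the protocol article bear on the end point.

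- The list of primary outcomes, at the end of *Estimating the adverse effects of using incentives to achieve quitting*, names "smoking cessation at delivery".
- *Smoking cessation: assessed on two occasions* heads outcome (a) "between six weeks after enrolment in the scheme and prior to childbirth". Criterion (a)i requires "self reported smoking cessation for at least 24 hours at six weeks after enrolment in the scheme", with a CO check. Criterion (a)ii requires "self reported complete abstinence from 6 weeks after enrolment to 36 weeks gestation, validated by salivary cotinine less than 15 ng/ml at 36 weeks". It continues: "In addition, there must be no reported lapses and a record that all CO readings taken between these dates indicate non-smoking status". The dates meant are six weeks after enrolment and 36 weeks gestation.
- *Measuring smoking cessation* says cotinine will be used "from saliva samples to verify abstinence both at delivery and at six months post-partum". It describes cotinine testing in pregnancy as happening once, at around 28 weeks.
- *Enrolment* and *Biological samples taken to assess quitting and gaming* list four saliva samples: 28 weeks, 36 weeks, two days after delivery, and six months post-partum. The outcome definition uses the two-day sample only for outcome (b).
- *Exclusion criteria* removes from the cessation rate only women who have died, moved untraceably, miscarried or had a stillbirth. No upper gestational limit on entry is given. The Table 2 footnote foresees late starts: "A woman starting quitting later in pregnancy would start with Visit 1 in terms of the incentive on offer".

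**The concern.** This is one of only two primary outcomes, and its label, heading and verification rule do not share a time point. Two analysts working from the same article could classify the same woman differently. One would follow the heading and fail a woman who reports smoking at 38 weeks. The other would follow (a)ii and count her as abstinent.

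The time point also matters for interpretation. *Public attitudes* and *Data analysis* set the result against the hospital's previous year, when smoking was recorded at booking (500 women) and at delivery (483 women). A rate that closes at 36 weeks does not match that time point.

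The rule also leaves two groups without a workable outcome: women with a live birth before 36 weeks, and women who enrol late in pregnancy.

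**Working it through.** **1. The plan's own figure.** From *Precision estimation*: quit rate 24%, n = 150, so 0.24 × 150 = 36 expected quitters. The 95% half-width is 1.96 × √(0.24 × 0.76 / 150) = 0.0683, or 6.8 points. The stated ±7% is reproduced.

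**2. Where the window closes relative to the visit schedule.** Table 2 takes a start at about 12 weeks gestation.
- Visit 15 (24 weeks after quitting): 12 + 24 = 36 weeks.
- Visit 16 (28 weeks after quitting): 12 + 28 = 40 weeks.

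So the scheme schedules a CO test after the window in (a)ii has closed. That criterion makes no use of it.

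**3. Three cases under (a)i and (a)ii.**
- *Smoking between 36 weeks and birth.* The no-lapse and CO requirements apply only between the two stated dates. Under (a)ii such smoking does not disqualify, even if it is reported or shown at Visit 16. Under the heading of outcome (a), it does.
- *Live birth before 36 weeks.* No 36-week saliva sample can exist, so (a)ii cannot be met as written. These women are not among the exclusions, and no other rule is given for them.
- *Late enrolment.* The window runs from enrolment + 6 weeks to 36 weeks, and 36 − 6 = 30. At 30 weeks its length is zero, and after 30 weeks it is reversed. Failure is certain only for enrolment after 36 weeks (no 36-week sample) or for birth within six weeks of enrolment ((a)i cannot be met before birth). Between 30 and 36 weeks the outcome is undefined.

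**4. Illustrative size.** The documents give neither a relapse rate from 36 weeks to birth nor the share of births before 36 weeks. Both are assumptions here.

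Late relapse at rate r among the 36 quitters, rate at delivery = 36(1 − r)/150:

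| r | Quitters at delivery | Rate |
|---|---|---|
| 0 | 36.0 | 24.0% |
| 5% | 34.2 | 22.8% |
| 10% | 32.4 | 21.6% |
| 20% | 28.8 | 19.2% |

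The 36-week rule would therefore overstate abstinence at delivery by 1.2 to 4.8 points.

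If a share e of otherwise successful women has no 36-week sample and is counted as failing, the rate is 0.24(1 − e). At e = 2% it is 23.5%, and at e = 10% it is 21.6%. This error is 0.5 to 2.4 points and runs the other way.

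**5. Effect on the stated reading.** *Data analysis* asks whether the 95% interval includes 0%. At 19.2% the half-width is 1.96 × √(0.192 × 0.808 / 150) = 6.3 points, giving 12.9% to 25.5%. The reading is unchanged.

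**The case against.** The strongest defence is that 36 weeks is a reasonable late-pregnancy end point. Table 1 describes a comparable UK trial whose incentives run to 34-38 weeks gestation. The group enrolling from 30 weeks is probably small, because *Smoking cessation interventions in pregnant women* puts booking usually at 8 to 12 weeks and *Recruitment and screening* has women phoned within one working day of receipt of the referral. The shifts rest on assumed rates, partly offset each other, and hardly touch precision. All of this stands, and it limits the size of the point. It does not remove the conflict: nowhere does the article say that 36 weeks stands for delivery, and *Measuring smoking cessation* places the cotinine check at delivery.

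A reader might infer three stronger things that the text does not support.

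- *That late relapsers are, by settled rule, counted as quitters.* The heading of outcome (a) would itself exclude a reported late lapse. The text contradicts itself and does not fix that rule.
- *That all late enrollees are bound to fail.* This is certain only in the two situations given in the working. The Table 2 footnote also concerns when a woman starts quitting, whereas the outcome clock runs from enrolment.
- *That the two-day post-delivery cotinine should become a condition of the primary outcome.* By the article's own account cotinine reflects the preceding few days, and *The incentive scheme* says many mothers deliberately return to smoking after pregnancy. The sample could fail women who were abstinent until birth. Judging women on it alone would also replace prolonged abstinence with point prevalence.

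**Conclusion.** The inconsistency is real and sits in a primary outcome. The label, the heading and the statement on cotinine verification point to delivery. The operative criterion ends its window, its lapse and CO requirements and its verification at 36 weeks. Live births before 36 weeks cannot meet that criterion and are not excluded. Enrolment from 30 weeks leaves the outcome undefined.

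The numerical effect is modest and uncertain. With an assumed 5-20% late relapse among 36 expected quitters, 24% at 36 weeks corresponds to 22.8-19.2% at delivery, and missing 36-week samples from early births pull the reported rate the other way. The planned comparison with 0% is not affected. What is at stake is what the headline rate means and whether women are classified reproducibly.

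**What to change.** Reconcile *Measuring smoking cessation*, *Smoking cessation: assessed on two occasions* and the list of primary outcomes to one end point, in one of two ways.

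1. Keep the label. Extend the requirement of no reported lapses and all CO readings negative from 36 weeks to delivery, and keep the 36-week cotinine as the biochemical check. Report the two-day post-delivery cotinine, already collected, as a sensitivity analysis, noting that it may reflect smoking resumed after birth.
2. Keep the criterion. Rename the outcome prolonged abstinence to 36 weeks throughout, and say that it is not on the same time point as the hospital's figure at delivery.

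In either case:
- State that for live births before 36 weeks the window closes at delivery, with the two-day sample replacing the missing 36-week cotinine. The no-lapse and CO requirements still apply up to the birth.
- State how women enrolling from 30 weeks are classified.
- Correct the account of cotinine testing in *Measuring smoking cessation* to match the four-sample schedule.

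The cost is wording. No new visit or assay is needed, since the late CO reading and the two-day sample are already planned. Under the first option the headline rate will be slightly lower.

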The incentive scheme ‘starts again’ after birth for two reasons. First, women who have smoked during pregnancy may now wish to become abstinent to avoid affecting their child’s health through environmental tobacco smoke and/or breast milk. For them, this incentive frequency mirrors that during pregnancy for the initial days of a quit attempt. Second, we know that return to smoking after pregnancy is a deliberate choice by many mothers when the incentive to be abstinent due to carrying a baby attached by a placenta is removed. The incentive structure is designed to reward a woman frequently during the initial postpartum period to maintain the incentive to be abstinent when the natural incentive to do so has gone.

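### At day 2 after delivery, outcome (b) i checks a 24-hour quit claim with a test that looks back further, so truthful recent quitters may fail it and may be counted as false reporters

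*Protocol article*

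**What the plan says.** All references are to the protocol article.

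- **Opening of outcome (b)** (Smoking cessation: assessed on two occasions, item (b) i). The woman must give a report of "self reported smoking cessation for at least 24 hours two days after delivery", validated by CO of at most 6 ppm and by "salivary cotinine less than 15 ng/ml, in keeping with local practice".
- **Opening of outcome (a)** (same section, item (a) i). This asks for "self reported smoking cessation for at least 24 hours at six weeks after enrolment in the scheme", validated by CO alone. The section adds: "This definition gives women a cessation induction period of up to six weeks". That period runs from enrolment, and no equivalent is stated after delivery.
- **What the tests see** (Measuring smoking cessation). The section gives the CO breath test a look-back of one to four hours. Of the other test it says: "cotinine analysis from blood, urine or saliva samples can measure exposure to smoking in the preceding few days".
- **Why the scheme restarts after birth** (The incentive scheme). The first of two reasons is that "women who have smoked during pregnancy may now wish to become abstinent". The second is to help women who are already abstinent to stay so.
- **Use of the day-2 sample** (Estimating the adverse effects of using incentives to achieve quitting). False reporting to gain an incentive is one of two primary outcomes. It is estimated by checking CO records and self-report against cotinine at four time points, one of which is two days after delivery.
- **Continuation of outcome (b)** (item (b) ii). The window is "self reported complete abstinence from two days after enrolment to six months postpartum", although the item's heading starts it at childbirth.

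**The concern.** The claim at day 2 covers 24 hours, while the test that validates it can cover several days and so can reach back to delivery or before. A woman can meet the self-report and CO conditions truthfully and still fail on cotinine left from smoking that she does not deny.

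Two results are exposed. First, outcome (b) has no later point of entry, so a woman failed at day 2 is not counted as abstinent at six months however long she then abstains. Secondly, the same sample feeds a primary outcome. The section Biological samples taken to assess quitting and gaming treats a positive saliva result as proof of smoking, and no rule sets recent quitters apart. A truthful 24- to 48-hour quitter with residual cotinine could therefore enter the false-reporting numerator. The first error lowers postpartum abstinence and the second raises false reporting.

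**Working it through.** **Plan's own figures.** The protocol gives no number for this point: no cotinine half-life, no baseline saliva level, and no expected share of women stopping at birth. The half-widths under Precision estimation reproduce as 1.96 × √(0.30 × 0.70 / 500) = 4.02 points (stated ±4) and 1.96 × √(0.24 × 0.76 / 150) = 6.83 points (stated ±7). Neither enters the argument or is changed by it.

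**Step 1: set the windows side by side.**

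| Item | Claim | Test | Look-back stated in the protocol |
|---|---|---|---|
| (a) i | at least 24 h | CO | 1 to 4 h |
| (b) i | at least 24 h | CO and salivary cotinine | 1 to 4 h; few days |

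In (a) i the test looks back less far than the claim. In (b) i the cotinine test looks back further.

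**Step 2: see whether residual cotinine could matter at 15 ng/ml.** Assume first-order decay, level(t) = baseline × 0.5^(t / half-life). The half-life (9 to 20 h) and baseline (100 to 300 ng/ml) are assumptions. The two times are 24 h, the shortest claim allowed, and 48 h, a woman who stopped at delivery and is sampled on day 2. The highest baseline that falls to 15 ng/ml by time t is 15 × 2^(t / half-life).

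| Half-life (h) | Level at 24 h, baseline 100 to 300 | Level at 48 h, baseline 100 to 300 | Highest passing baseline, 24 h | Highest passing baseline, 48 h |
|---|---|---|---|---|
| 9 | 15.7 to 47.2 | 2.5 to 7.4 | 95 | 605 |
| 12 | 25.0 to 75.0 | 6.25 to 18.8 | 60 | 240 |
| 17 | 37.6 to 112.8 | 14.1 to 42.4 | 40 | 106 |
| 20 | 43.5 to 130.6 | 18.9 to 56.8 | 34 | 79 |

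At 24 h every case in the assumed range is above 15 ng/ml, the lowest only just (15.7). At 48 h the range is 2.5 to 56.8 and straddles the cut-off: all pass with a 9 h half-life, all fail with 20 h, and results are mixed between. A baseline of 50 passes at 48 h for every half-life (1.2 to 9.5 ng/ml). At 24 h it passes with half-lives of 9 and 12 h (7.9 and 12.5) and fails with 17 and 20 h (18.8 and 21.8).

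The time to reach 15 ng/ml is half-life × log2(baseline / 15). It runs from 9 × log2(100/15) = 24.6 h to 20 × log2(300/15) = 86.4 h, which agrees with a look-back of a few days.

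**Step 3: see who could be miscounted as a false reporter.** The protocol describes the self-report in three ways: at least 24 hours (item (b) i), complete abstinence since last contact (The incentive scheme), and simply not smoking (the visit procedure under Visits). Take a woman who smoked until delivery, stopped then, and was last seen before delivery. She can truthfully make the first and third statements but not the second. If she makes the second, a positive cotinine rightly marks it false. If she makes only the first or third, a positive cotinine would mark a true report as false. The protocol does not say which statement is set against the day-2 cotinine.

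**The case against.** The case for the present wording has force.

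- **The asymmetry is declared.** The section says the two outcomes need different measures and cites local practice for the cotinine test. A strict start suits an outcome of prolonged abstinence from childbirth. It also suits the second reason for the restart, preventing relapse. This stands, so the text does not prove a contradiction. It leaves the intended population of (b) unstated.
- **The restart concerns payment, not the outcome.** Vouchers depend on self-report and CO, and saliva results never lead to refusal. Women who quit at birth are not shut out of the scheme. This also stands; what is at issue is how they are counted.
- **The declaration for payment is abstinence since last contact.** This narrows the group that could be wrongly called false reporters, as Step 3 shows, but does not empty it.
- **Dropping cotinine at day 2 has a price.** Under Unintended perverse effects of incentive schemes the protocol cites a study in which abstinence was 38% against 5% by CO but 7% against 2% by cotinine. It also notes that a few hours without smoking can pass a CO test. This is a good reason not to make CO alone the main criterion.

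A reader might infer that women who stop at delivery cannot pass, or that such quits can never count. The protocol does not support that: it says only that cotinine can reflect a few days, and the 48-hour range above includes clear passes. A reader might also try to size the bias by combining the 24% quit rate, the 70% postnatal relapse rate and a guessed share quitting at birth. That share is not in the protocol, the relapse figure is not for women paid to abstain, and the sum would need every such woman to fail at day 2.

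**Conclusion.** The mismatch of windows is real on the protocol's own text. Women who truthfully stop at or just after delivery may fail (b) i on residual cotinine. They may also be counted as false reporters at one of the four time points of a primary outcome. The likely direction is downward for postpartum abstinence and upward for false reporting.

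The size cannot be derived. Failure at 24 hours holds throughout the assumed range of 100 to 300 ng/ml and 9 to 20 h, but not for lower baselines; at 48 hours the result depends on both assumptions. Outcome (b) is secondary and the study plans no formal tests, so the stronger reason to act is the false-reporting estimate, which can be put right with samples already planned.

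**What to change.** 1. **Record the claimed quit date at the day-2 visit**, and state which self-report is compared with cotinine.
2. **False-reporting analysis.** Fix the cotinine window in hours before analysis. Count a positive day-2 cotinine as false only when the claimed abstinence is longer than that window, including any declaration of abstinence since last contact. Report more recent quitters separately.
3. **Outcome (b).** Reconcile The incentive scheme, Measuring smoking cessation and item (b) i. Either state that (b) measures abstinence already established before delivery, or add a sensitivity estimate that opens (b) with self-report plus CO, as (a) i does, and keeps the six-month cotinine check.
4. **Item (b) ii.** Correct the start of the window, now given as two days after enrolment, to agree with the childbirth heading.

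The cost is one recorded date, one analysis rule and some wording, with at most one extra estimate. No new samples are needed and the stated precision is unaffected. The downside is small: in the sensitivity estimate the start of (b) rests on a shorter-window test, so that estimate should stand beside the cotinine-based one and not replace it.
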